### Mersey care telehealth service

The MCTS is a complex, clinician-led remote monitoring intervention designed for patients with long-term conditions and/or an elevated risk of deterioration. The service was initially established in Liverpool in 2011 and delivered through an internally managed Mersey Care platform. In November 2017, following a tripartite partnership between Liverpool Clinical Commissioning Group (CCG), Mersey Care, and Docobo, the service transitioned to the Docobo remote monitoring platform. The service was subsequently expanded to additional localities, including St Helens (September 2021), Sefton (July 2022), Wirral (May 2023), and Cheshire West (February 2024). Across all localities, eligible patients include those with COPD, HF, and diabetes, as well as individuals with any combination of two of these conditions.

The service includes digital or telephone-supported submission of physiological observations and symptom data, asynchronous review by the telehealth team, patient education, self-management support, telephone contact, and escalation to primary, community, specialist, or urgent care services where clinically indicated. Patients may be monitored at varying levels of intensity depending on their condition, risk profile, clinical needs, and care pathway, with monitoring arrangements reviewed regularly by clinical staff. The intervention should therefore be understood as a whole-service model rather than the isolated effect of a digital platform. Consequently, any observed impact on hospital admissions, outpatient activity, or other healthcare utilisation outcomes may reflect the combined effects of technology-enabled monitoring, clinician-led case management, escalation processes, and supported self-management.

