### Data

The study will use a cohort of monthly data from the Cheshire and Merseyside Secure Data Environment (CM-SDE), the NHS secure data environment that includes linked data across health and care services for all patients registered with a GP in Cheshire and Merseyside. We will use CM-SDE covering a period, 2018–2024 including linked data from the following datasets:

NHS

Primary care dataPrimary care prescribing dataTelehealth services data from the MC telehealth case management system.Secondary care data—Admitted Patient Care (SUS-APC)Community Services Data Set (CSDS)Mental Health Services Data Set (MHSDS)Emergency Care Data Set (ECDS)

Local Authority Adult Social Care

Adult Social Care Dataset (ASCD)

Open data—linked to Lower layer super output areas (LSOAs)

Indices of deprivation

All these datasets are available and can be linked within the CM-SDE. Patient characteristics will reflect individuals at the time of receiving telehealth service and so will correspond to the latest measurement taken during the study period 2018–2024. Table 2 summarises the details of outcome and exposure variables, definition criteria, and datasets from which the variable is derived that would be used in WP1 of the study.

**Table 2 TB2:** Exposure, covariates, and outcome variables for WP1.

Variable category	Variable	Definition/criteria	Data source
Primary exposure	MCTS enrolment	Active enrolment onto the Mersey Care Telehealth Service (Yes/No)	MCTS service dataset
Demographic and baseline characteristics	Age	Age at index date (≥18 years)	SUS-APC
	Sex	Male, Female, Other	SUS-APC
	Ethnicity	White British, Other White, Black, Indian, Pakistani, Bangladeshi, Chinese, Other Asian, Other ethnic group	SUS-APC
	Living alone	Yes/No	Primary Care
	Living with under-18s	Yes/No	Primary Care
	Household size	Number of people in household	Primary Care
	Geography	LSOA 2011	SUS-APC
	Deprivation	IMD 2019	SUS-APC
	Frailty	Fit, mild, moderate, severe frailty	Primary Care
Clinical characteristics	Long-term conditions	Hypertension, cancer, diabetes, CVD, heart failure, CKD, asthma, COPD, depression, schizophrenia, bipolar disorder	Primary Care
Baseline healthcare utilisation	Emergency admissions (previous 12 months)	Count of emergency admissions before index date	SUS-APC
Outcomes	Unplanned emergency hospital admissions	Count of admissions during follow-up	SUS-APC
	A&E attendances	Count of attendances during follow-up	SUS-ECDS

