### Analysis

The study uses two quasi-experimental methods: IPTW-DiD and RD designs. These methods help to reduce the risk of selection bias due to systematic differences between those receiving and not receiving the intervention, in two ways.

The primary approach of the analysis is IPTW-DiD, which is specifically designed to adjust observed differences by reweighting individuals according to their probability of receiving treatment, thereby approximating a pseudo-population in which treatment is independent of observed confounders. The treated cohort will comprise patients who received telehealth, with treatment timing defined by the first quarter in which telehealth was received; patient-quarter observations from this quarter onwards will be considered post-intervention. For untreated patients, comparable index quarters will be assigned to define the pre- and post-intervention periods.

The initial analytic cohort will be restricted to patients aged 50 years or above with at least one relevant long-term condition linked to the telehealth packages: COPD, diabetes, or HF. These eligibility criteria will be applied to both treated and untreated patients to ensure that the control group comprises individuals with a realistic probability of receiving the intervention. To avoid interpreting unobserved quarters as zero healthcare utilisation, the initial analysis will use a balanced panel of patients observed in all 24 quarters across the 6-year study period. The potential selection introduced by excluding patients who die, move away, or register with a GP partway through the study period will be explored in sensitivity analyses.

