A treatment model will calculate the likelihood of each patient receiving the intervention using baseline socio-demographic variables, comorbidity measures, and 12-month cumulative pre-intervention healthcare utilisation, such as unplanned emergency admissions. For variables that may change over time, baseline or pre-intervention values will be used. Stabilised IPTW weights (Austin and Stuart, 2015) will be used in the DiD model to balance measured baseline covariates and reduce the influence of extreme weights. Covariate balance, weight stability, overlap/common support, effective sample size, and the plausibility of the conditional parallel-trends assumption will be assessed using weighting diagnostics and pre-intervention outcome trends. Comprehensive sensitivity analyses will be performed to evaluate the robustness of all estimates.

To manage the potentially large untreated population, the above eligibility restrictions will be applied before weighting. If the remaining comparison cohort is still too large for the available computing environment, a 5:1 propensity-score matched comparison cohort based on baseline characteristics may be constructed before applying the weighting approach; this will be reported as a computational sensitivity analysis.

Additionally, the RD design (Thistlethwaite and Campbell, 1960) will serve as a secondary complementary analysis, subject to the availability of a documented Johns Hopkins ACG risk score eligibility threshold (NHS England, 2025d) and sufficient observations close to that threshold. Threshold values, temporal changes, and geographical variations will be documented. As RD estimates a local effect among patients close to the eligibility threshold, its findings will be interpreted alongside, rather than as direct confirmation of, the IPTW-DiD estimates.

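### The Work package 1 data window, 24-quarter panel, 12-month lookback and first-use rule do not fit together: no earliest index quarter is stated and telehealth use before 2018 is not handled

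*Protocol article*

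**What the plan says.** **Window.** The Data section of Work package 1 states: "We will use CM-SDE covering a period, 2018–2024 including linked data from the following datasets". The telehealth service data are on that list. The same section speaks of "the latest measurement taken during the study period 2018–2024", so the study period carries the label 2018–2024. No months are given.

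**Panel.** The Analysis section says that "the initial analysis will use a balanced panel of patients observed in all 24 quarters across the 6-year study period".

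**Lookback.** The treatment model uses "12-month cumulative pre-intervention healthcare utilisation, such as unplanned emergency admissions". Table 2 likewise lists emergency admissions in the 12 months before the index date as the baseline utilisation covariate.

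**Exposure.** The treated cohort has "treatment timing defined by the first quarter in which telehealth was received", and that quarter and all later ones count as post-intervention. The Work package 1 Methods section sets the index date at the start of active monitoring. Comparators are eligible patients, alive and registered in the same quarter, who did not enrol. Neither section mentions earlier use.

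**Service history.** "The service was initially established in Liverpool in 2011 and delivered through an internally managed Mersey Care platform". It moved to the Docobo platform in November 2017. Patients may be re-enrolled after discharge.

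**The concern.** Each rule is reasonable alone, but together they leave the primary cohort undefined at its early edge.

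- **Panel.** A patient must be observed in every panel quarter to enter the initial analysis, so the dates decide who is in it. Six years and 2018–2024 inclusive are different lengths.
- **Lookback.** The Johns Hopkins ACG score is not available for the wider eligible population, and the protocol names prior utilisation among the proxies for baseline risk. If part of the 12 months falls before the data begin, the admission count is truncated and the weights adjust for less than they claim.
- **Earlier use.** A service that began in 2011, with service data listed from 2018, may have past users whom the data do not identify. A continuing or returning user dated to a first quarter inside the window has a pre-period that is already exposed. A user discharged before 2018 looks like a never-user. The only locality with a documented service before 2018 is Liverpool, which holds 2,000 of the 2,350 commissioned places (85%).

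**Working it through.** **1. The plan's own figure.** 6 years × 4 = 24 quarters, so the panel figure is consistent in itself. 2018–2024 inclusive is 7 × 4 = 28 quarters. The difference is 28 − 24 = 4 quarters.

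**2. What the possible panels imply.** The article does not choose between these.

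| 24-quarter panel | Consequence |
|---|---|
| Q1 2018–Q4 2023 | Cheshire West, documented as opening in February 2024, supplies no treated patients. No data precede the panel if the data also open in Q1 2018. |
| Q1 2019–Q4 2024 | 2018 can supply a full lookback for every in-panel index quarter. Anyone first treated in 2018 is treated in all 24 quarters and has no pre-period in the panel. |
| Mid-2018 to mid-2024 | Fits both labels loosely and can include some Cheshire West users. The lookback depends on when the data start. |

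**3. Lookback by index quarter, if data and index quarters both open in Q1 2018.** Quarters available before index quarter q = q − 1. A full lookback needs q − 1 ≥ 4.

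| Index quarter | Prior quarters | Full 12 months? |
|---|---|---|
| Q1 2018 | 0 | No, and no pre-period |
| Q2 2018 | 1 | No |
| Q3 2018 | 2 | No |
| Q4 2018 | 3 | No |
| Q1 2019 | 4 | Yes |

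Affected share of index quarters: 4/24 = 16.7%, or 4/28 = 14.3%. This is a share of quarters, not of patients.

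**4. Earlier users, with service data from 2018 only.**
- On the service across the start of 2018: first observed quarter is Q1 2018, which is false.
- Discharged before 2018, re-enrolled later: first observed quarter is the re-enrolment, which is false.
- Discharged before 2018, not re-enrolled: no record, so eligible as an untreated comparator.

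Keeping 2018 as a lookback year does not identify the last two groups.

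**5. Illustration of truncation, under assumed inputs.** I simulated 4 million patients with no treatment effect. Admissions are gamma-Poisson with mean 0.6 a year and shape 0.7. The log-odds of enrolment start at −3.5 and rise by 0.4 to 0.7 per admission in the prior year. Comparators are standardised to the treated on the count that the truncated lookback shows.

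| Lookback | Post-index rate ratio (true value 1.00) |
|---|---|
| 12 months | 1.00 |
| 9 months | 1.06–1.11 |
| 6 months | 1.15–1.27 |
| 3 months | 1.30–1.54 |

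These ratios apply within the truncated cohorts only, before any differencing. Suppose Q1 2018 drops out for want of a pre-period and all other index quarters weigh equally. The pooled log ratio is then the sum of the logs for 3, 6 and 9 months, divided by 23 or 27. That gives a pooled ratio of about 1.02–1.03. None of the inputs comes from the protocol.

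**The case against.** **The article does not say that 2018 enrolees are indexed.** A reader might infer that patients are admitted from the first day of the window. That is an inference from silence. The four spare quarters equal a 12-month lookback, so 2018 may be an unstated run-in year, and then no in-panel enrolee lacks the lookback. This stands, and the lookback point is therefore conditional. It does not remove the need to state the dates, because both sections use the term study period, one labels it 2018–2024, and the other gives it six years.

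**First use may mean true first use.** Read literally, the exposure rule and the index date at the start of active monitoring would screen out earlier users. That works only if the service dataset carries pre-2018 start dates, which the article does not say. The misdating is possible, not shown.

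**Such rules may sit in a fuller document.** A condensed article may omit a washout rule. But this article itself fixes the window, the panel, the lookback and the exposure rule, and those four do not fit together as stated.

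**Size.** A reader might set the simulated ratios against the target relative risk of 0.85 and conclude that the bias is as large as the effect sought. The documents do not support that: the ratios concern the truncated cohorts under invented inputs, and the target concerns the whole study.

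**Site.** A reader might also infer that every affected enrolee is from Liverpool. Table 1 dates Docobo use in the other localities from November 2017 or January 2018, and its footnote warns that true enrolment periods may differ from the documented dates.

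**Conclusion.** The point holds in a conditional form. The disagreement between 2018–2024 and 24 quarters over six years is on the page and needs no assumption beyond reading the years inclusively. The lookback gap affects four index quarters (17% of 24 or 14% of 28) if data and index quarters both open in Q1 2018, and none if 2018 is reserved as lookback. The earlier-user problem is the more durable half, since a lookback year does not cure it. It rests on the service data not holding pre-2018 start dates.

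The overall bias cannot be quantified, because enrolments by year and the number of pre-2018 users are not given. The documents also do not settle whether 24 or 28 quarters is right. The change is worth making before analysis because it is cheap and closes an avoidable source of bias in the primary estimate.

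**What to change.** 1. Reconcile the Data and Analysis sections by stating the start and end months of the data and of the panel. One possibility, if it is what is meant, is 2018 as lookback with a 24-quarter panel for 2019–2024. In that case, say whether the 2018 quarters also count as pre-period outcomes, since a Q1 2019 index would otherwise have a full lookback but no pre-intervention quarter in the panel.
2. In both groups, admit index quarters only from at least four quarters after the data start.
3. Exclude patients with any earlier use of the service from both groups, using service records, including those of the platform used before November 2017 where held.
4. If those records are not held, state that pre-2018 use is unobserved and run a sensitivity analysis in the localities that opened later, after confirming their true first enrolment dates.

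The cost is a few sentences and a cohort filter. First-year enrolees leave the primary analysis but can be kept in a sensitivity analysis. The analysis in step 4 will be small: the later localities hold 50 + 100 + 100 + 100 = 350 of 2,350 commissioned places (15%).

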The primary exposure is active enrolment onto the MCTS. Referral alone will not constitute exposure, as not all referred patients commence telehealth monitoring. For enrolled patients, the index date will be defined as the date on which active telehealth monitoring begins. To account for temporal variation in healthcare utilisation and service delivery, telehealth enrolment dates will be grouped into calendar quarters (Q1: January–March; Q2: April–June; Q3: July–September; Q4: October–December). Comparator patients will be selected from quarterly eligibility snapshots comprising individuals who were eligible for MCTS, alive, and registered during the same quarter but who did not enrol onto the service. Calendar quarter will be used as an exact matching variable within the propensity score matching process, ensuring that telehealth participants are compared only with eligible non-enrolled patients observed during the same time period. Additional demographic, clinical, risk, and baseline healthcare utilisation variables will be incorporated into the matching procedure. This approach aims to minimise temporal bias arising from changes in healthcare utilisation, seasonal pressures, COVID-19 recovery effects, admission practices, and service delivery over the study period. The primary analysis will therefore estimate the effect of active enrolment onto MCTS compared with eligible non-enrolment during the same calendar quarter. Findings should be interpreted as representing the effect of the telehealth service model as delivered in routine practice rather than the effect of referral alone or any individual intervention component.

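### WP1 counts the whole calendar quarter of enrolment as post-intervention although monitoring starts part-way through it, which dilutes the primary estimate, most at short horizons

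*Protocol article*

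**What the plan says.** All places are in the Protocol article, Work package 1.

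- **Methods (exposure).** For enrolled patients, "the index date will be defined as the date on which active telehealth monitoring begins". The same paragraph then says that "telehealth enrolment dates will be grouped into calendar quarters", with fixed boundaries (January–March and so on).
- **Analysis (primary approach).** The treated cohort has "treatment timing defined by the first quarter in which telehealth was received", and "patient-quarter observations from this quarter onwards will be considered post-intervention". Comparators, who have no enrolment date, are handled by assignment: "comparable index quarters will be assigned to define the pre- and post-intervention periods".
- **Table 2.** Baseline use in the previous 12 months is defined as "Count of emergency admissions before index date". The primary outcome is "Count of admissions during follow-up".
- **Analysis (treatment model).** The weights use 12-month cumulative utilisation described as pre-intervention, with no reference to the index date.
- **Data.** "The study will use a cohort of monthly data", so time can be cut more finely than by quarter.

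No washout, transition quarter or sensitivity analysis for the enrolment quarter is named. The article names a sensitivity analysis on panel selection and otherwise promises comprehensive ones without listing them.

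**The concern.** The article uses two time zeros. Exposure starts on a day, while the primary analysis starts the post-intervention period at the beginning of the calendar quarter containing that day. The days in between are outcome time under treatment by label but not in fact.

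Assigning comparators an index quarter makes the labels match, but it does not remove the problem. Comparators are untreated throughout their quarter, so only the enrolled group has mislabelled time. The planned check of pre-intervention trends cannot detect it, because the mislabelled weeks lie in the post period.

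At stake is the primary outcome, unplanned emergency admissions. The error weighs most on short horizons. Standard initial monitoring lasts up to 5 months, under two quarters. Work package 4 has a 6-month horizon and takes its resource use from this analysis, so the error could carry over if the same quarters are used there.

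**Working it through.** **The plan's own figures.** The panel length reproduces: 6 years × 4 = 24 quarters. The stated 80% power at a relative risk of 0.85 comes from a simulation whose base rate, significance level and correlation the article does not give. It can be neither reproduced nor disputed here, and 0.85 serves only as the reference effect.

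**Inputs**
- True relative risk after monitoring starts: 0.85 (Sample section), held constant.
- Enrolment dates uniform within the quarter (assumption). Mean untreated time is then 365.25/4/2 = 45.7 days, half the quarter.
- m = admission rate in the pre-enrolment part of that quarter, relative to the comparator rate (assumption, shown as a range).
- K = number of post quarters averaged, including the enrolment quarter (assumption; the article fixes no window).

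**Formula.** Set the comparator rate to 1 per quarter. The enrolled group has 0.5m + 0.5×0.85 in the enrolment quarter and 0.85 in each later quarter, so

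observed ratio = [0.5m + (K − 0.5)×0.85] / K = 0.85 + 0.5(m − 0.85)/K.

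For example, with K = 2 and m = 1: (0.5 + 1.5×0.85)/2 = 1.775/2 = 0.8875.

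| K | Untreated share of post time (0.5/K) | m = 1 | m = 1.5 | m = 2 | m at which the ratio is 1 |
|---|---|---|---|---|---|
| 1 | 50% | 0.9250 | 1.1750 | 1.4250 | 1.15 |
| 2 | 25% | 0.8875 | 1.0125 | 1.1375 | 1.45 |
| 4 | 12.5% | 0.8688 | 0.9313 | 0.9938 | 2.05 |
| 8 | 6.25% | 0.8594 | 0.8906 | 0.9219 | 3.25 |
| 12 | 4.2% | 0.8563 | 0.8771 | 0.8979 | 4.45 |

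The last column solves m = [K − (K − 0.5)×0.85]/0.5. A Poisson simulation at K = 1 and 2 agreed: 0.930 and 0.887 for m = 1, and 1.435 and 1.146 for m = 2.

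**Direction.** The second form of the formula shows the ratio moving above 0.85 whenever m exceeds 0.85, and below it only when m is less than 0.85, for example if patients tend to be out of hospital and stable when they start.

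**Effect of moving the start of post time alone.** Starting post time at the index date puts any pre-enrolment spike into the pre-period. With a 12-month pre-period and a doubled rate in its last 1.5 months, the pre-level is (10.5 + 1.5×2)/12 = 1.125 times its usual value. An unadjusted difference-in-differences ratio would then be 0.85/1.125 = 0.76, which overstates the benefit.

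**The case against.** The strongest objection is to size. Both m and K are assumptions. The panel spans 24 quarters and post time runs on from enrolment, so if many post quarters are averaged and m is near 1, the dilution is small: 0.856 against 0.85 at twelve quarters. The calculation is also a simple post-period ratio, not the planned weighted difference-in-differences. A generally higher risk among enrolled patients is not m = 2. Weighting on prior use and differencing should remove much of that, and m above 1 needs a short-lived rise beyond it. All of this stands, and it limits what can be claimed. It does not relabel the untreated weeks, and dilution at m = 1 needs no spike.

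Three stronger readings are tempting but not supported.

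- **The service's effect would be erased.** A doubled rate takes the ratio to about 1 over four quarters, but no four-quarter window is stated, and over twelve quarters m would have to reach 4.45. The 37% six-month risk used for case finding does not help: a base rate cancels from the ratio, and that threshold applies only from January 2024. Table 1 shows patients arriving largely through a population tool or step-down, neither described as triggered by an admission.
- **Admissions are counted twice, as baseline and as outcome.** This follows only if Table 2's index date means the day monitoring begins. If pre-intervention use ends before the enrolment quarter, as the Analysis section can be read, there is no double count. The wording is ambiguous; an error is not shown.
- **The bias must run against the service.** It does for m above 0.85, which includes the no-excess case, but the article gives no figure for m.

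A transition-quarter sensitivity analysis may exist in a document not shown. It would not change the primary rule stated here.

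**Conclusion.** The point holds as a defect in how the primary analysis defines time zero. The rule as written labels about half of each enrolled patient's first quarter as treated when it was not, assuming even enrolment within quarters.

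Without any pre-enrolment excess the cost is dilution: material over one or two quarters and slight over eight or twelve. With an excess the distortion could be much larger at short horizons, but its size rests on a multiplier the article does not supply. Confidence is high that the time is mislabelled, and moderate on size and direction.

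**What to change.** 1. In the primary analysis, treat the enrolment quarter, and the comparators' assigned index quarter, as a transition period excluded from both the pre- and post-intervention periods. Dropping it from the post period alone is not enough; it must not be moved into the pre-period either.
2. End the 12-month baseline utilisation window before that quarter, in both groups.
3. Reconcile the index definition across the Methods paragraph on exposure, Table 2 and the Analysis section, so that index date, index quarter, baseline and pre-intervention each have one meaning.
4. As a sensitivity analysis, build a panel counted from the index date using the monthly data, with comparator index dates assigned in the same way. Exclude the period just before the index from the pre-period, so that a pre-enrolment spike does not overstate benefit.

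**Cost.** One quarter of follow-up per patient. On average that includes the first 46 days or so of monitored time, roughly 1.5 of up to 5 months, which is why the index-anchored sensitivity analysis is worth having. A spike before an enrolment early in a quarter would still fall in the last pre-period quarter, where the planned trend check can show it. Otherwise the change is wording and a re-cut of data already held, and it should be settled before outcomes are analysed.

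### WP1 difference-in-differences: the pre-period is not limited to quarters after diagnosis and time since diagnosis is not balanced, so a difference in disease duration could appear as a service effect

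*Protocol article*

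**What the plan says.** In the Analysis section of Work package 1, the cohort is "restricted to patients aged 50 years or above with at least one relevant long-term condition linked to the telehealth packages". Neither the age limit nor the condition is dated relative to the panel or the index quarter. The same section says "the initial analysis will use a balanced panel of patients observed in all 24 quarters across the 6-year study period". For enrolees, "patient-quarter observations from this quarter onwards will be considered post-intervention"; for the others, "For untreated patients, comparable index quarters will be assigned to define the pre- and post-intervention periods". No start is stated for the pre-period.

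Three other provisions bear on the point:

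- The Methods section of Work package 1 draws comparators from "individuals who were eligible for MCTS, alive, and registered during the same quarter but who did not enrol onto the service". This fixes their status in the index quarter.
- Table 2 lists the clinical covariates as "Hypertension, cancer, diabetes, CVD, heart failure, CKD, asthma, COPD, depression, schizophrenia, bipolar disorder", with no onset date or duration.
- The treatment model uses socio-demographic variables, comorbidity measures and "12-month cumulative pre-intervention healthcare utilisation, such as unplanned emergency admissions".

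The Analysis section also plans to check conditional parallel trends using outcome trends before the intervention. The Sample section gives the target effect as a relative risk of 0.85.

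**The concern.** A condition that qualifies a patient at the index quarter may have begun part-way through the panel. On the natural reading, a patient who enrols late has up to about five years of pre-period, part of which may precede the disease. If admissions are lower before diagnosis, those quarters pull the pre-period average down.

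This does no harm if it happens equally in both groups. If enrolees were diagnosed more recently than comparators, their before-to-after rise is larger and a null service looks harmful. If they were diagnosed earlier, a null service looks beneficial.

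Matching the last 12 months of admissions does not prevent this, because the imbalance lies in earlier quarters. A condition recorded as present carries no information on when it began. A difference in duration is plausible: the description of the service says patients were found through risk prediction, existing caseloads, referral and clinical judgement, that case finding changed in January 2024, and that the risk score is not available for selecting or matching comparators. The primary outcome under the primary method is at stake.

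**Working it through.** **Panel.** 6 years × 4 = 24 quarters, which agrees with the article. With an index in quarter 21, 20 quarters (5 years) precede it.

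**Closed form, null service.** Let the admission rate be r before diagnosis and k·r after it, and let f be the share of pre-period quarters that follow diagnosis. All post-period quarters follow diagnosis. The mean pre-period rate is r[1 + (k − 1)f], so

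apparent rate ratio = [1 + (k − 1)f(comparator)] / [1 + (k − 1)f(enrolee)].

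Take a 16-quarter pre-period, enrolees diagnosed 8 quarters before index (f = 0.5) and comparators at least 16 quarters before (f = 1):

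- k = 1.25: 1.25 / 1.125 = 1.11
- k = 1.5: 1.5 / 1.25 = 1.20
- k = 2: 2 / 1.5 = 1.33

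Exchanging the groups gives 0.90, 0.83 and 0.75. With durations spread out (means of 12 and 20 quarters, minimum 4) the ratios are 1.03, 1.06 and 1.09, or 0.97, 0.95 and 0.92 in reverse. With equal durations the ratio is 1.00, even though quarters before diagnosis are counted.

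**Simulation with weighting, null service.** Inputs, all assumed except the panel length: 200,000 patients per group; 24 quarters; index uniform over quarters 9 to 21; gamma time since diagnosis (shape 2) with a 1-year minimum; gamma frailty; Poisson admissions at 0.5 per year after diagnosis and 0.1, 0.25 or 0.4 before. Comparators are reweighted to the enrolees on the admission count of the last four quarters. This simplifies the planned stabilised weights. The apparent ratio is (enrolee post rate / pre rate) / (comparator post rate / pre rate).

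| Mean years since diagnosis, enrolee v comparator | 0.1 before | 0.25 before | 0.4 before |
|---|---|---|---|
| 2 v 3 | 1.23 | 1.11 | 1.04 |
| 2.5 v 3 | 1.09 | 1.05 | 1.02 |
| 3 v 4 | 1.11 | 1.06 | 1.02 |
| 3 v 3 | 1.00 | 1.00 | 1.00 |
| 4 v 3 | 0.90 | 0.94 | 0.97 |
| 3 v 2 | 0.81 | 0.89 | 0.96 |
| 5 v 6 | 1.02 | 1.01 | 1.01 |
| 6 v 5 | 0.97 | 0.98 | 1.00 |
| 7 v 8 | 1.01 | 1.01 | 1.00 |
| 8 v 7 | 0.99 | 0.99 | 0.99 |

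The extremes depend somewhat on the assumed spread of durations: 2 v 3 years at a rate of 0.1 gave 1.18 to 1.24, and 3 v 2 years gave 0.81 to 0.85.

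**Two remedies compared in the same simulation.**

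- Limiting the pre-period to quarters after diagnosis gave 0.99 to 1.01 when the rate after diagnosis was constant. With a peak in admissions just after diagnosis, errors of about 6% remained, and about 10% when the rate was assumed to double for the first year.
- Adding time since diagnosis to the weights while keeping all 24 quarters stayed within about 2% of 1.00 in every scenario, with or without the peak.

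**The case against.** A reader might infer that the plan expressly counts every earlier panel quarter as pre-intervention. It does not say so. The balanced panel is justified by a different aim, not reading unobserved quarters as zero use, and the full protocol or analysis plan may fix the start of the pre-period. That stands, and the point is therefore about what the written rules admit. It does not remove the point: panel length, split and cohort rule are all stated, and none keeps out quarters before diagnosis.

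A reader might also infer that the estimate will be biased, perhaps by as much as the whole planned effect. The documents support neither. Bias needs durations that differ after weighting and admissions that change around diagnosis; the article shows neither and gives no direction. Ratios near 0.85 appear only with short mean durations and low rates before diagnosis.

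The planned trend check is a real safeguard in the worst cases. With durations of 3 v 2 years and a rate of 0.1 before diagnosis, the weighted enrolee-to-comparator ratio of admissions by successive year before index was 1.00, 1.23, 1.77, 1.81 and 1.45, which would be plain to see. At a rate of 0.25 it rose only to 1.28. The check can show the divergence, but it does not correct it, and the section names no alternative analysis for that case.

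The objection to giving up the balanced panel also stands. A pre-period with patient-specific starts loses the balance the authors chose and does not fully work if admissions peak after diagnosis. It belongs in a sensitivity analysis.

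**Conclusion.** The concern holds in conditional form. The text as it stands lets quarters before diagnosis into the pre-period, and nothing in Table 2 or the treatment model balances disease duration. Eligibility at index, the condition list and the 12-month admission total do not do so.

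With the assumed rates and a difference of 0.5 to 1 year, a null service shows a ratio of about 0.81 to 1.24 at mean durations of 2 to 4 years. At 5 to 8 years it shows about 0.97 to 1.00 if enrolees were diagnosed earlier and about 1.00 to 1.02 if later. Set against a planned ratio of 0.85, this ranges from serious to negligible. Which applies depends on durations that the article does not give. This is a weakness worth closing in the primary analysis, not a demonstrated error in its result.

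**What to change.** In the Analysis section of Work package 1, add time since first qualifying diagnosis (COPD, diabetes or heart failure), measured at the index quarter, to the treatment model. Keep the balanced panel, and report covariate balance on this variable with the other weighting diagnostics.

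As a sensitivity analysis, repeat the difference-in-differences with the pre-period limited, in both groups, to quarters after the patient first met the condition and age criteria.

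The cost is one derived variable, on the assumption that diagnosis dates are held in the primary care data already listed, and shorter, unbalanced pre-periods in the sensitivity analysis only. No new data collection is needed if that assumption holds.
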